# 1      **PROTOCOL SYNOPSIS**

**Name of Sponsor/Company:**

Kaleido Biosciences, Inc.

**Name of Finished Product:**

Study product (SP) KB109 (spray-dried, synthetic oligosaccharide food composition)

**Name of Substance Investigated:**

KB109

**Title of Study:**

A Randomized, Open Label, Prospective, Parallel Group Study to Assess the Natural History of COVID-19 and Effects of KB109 in Addition to Supportive Self Care (SSC) Compared to SSC Alone on Measures of Health in Non-hospitalized Patients with Mild-to-Moderate COVID-19

**Study Rationale:**

The COVID-19 pandemic threatens individuals, societies and healthcare systems around the world. Host immunity contributes to the susceptibility as well as the progression of infectious disease and patient outcomes. Clinical studies and *ex vivo* experiments using human fecal samples have demonstrated that commensal bacteria selectively ferment proprietary oligosaccharide mixtures to promote their growth and produce metabolites such as the short-chain fatty acids (SCFAs) including acetic, propionic, and butyric acid. SCFAs modulate host inflammation, control adaptive immunity, and promote immune tolerance in the gut as well as systemically ([Thaiss 2016](#); [Schirmer 2016](#)). In particular SCFAs and SCFA-producing taxa have been linked to reduced risk of acquiring viral infections (including corona-viral infections) in at-risk populations (e.g., Hematopoietic stem cell transplantation [HSCT] patients, [Haak 2018](#)). Studies in mice have demonstrated that SCFAs and SCFA-producing microbial taxa induce virus-specific CD4+ and CD8+ T cells, interferon type I, and antibody responses involved in the reduction of viral infection severity ([Ichinohe 2011](#); [Trompette 2018](#)). Data has also shown that protection against Respiratory Syncytial Virus (RSV) infection can be conferred by acetate, a metabolite produced by the intestinal microbiota, through induction of interferon (IFN)- $\beta$  in the lung through GPR43 and IFNAR-mediated pathways ([Antunes 2019](#)). In addition, SCFAs have also been reported to influence macrophage functionality to mitigate neutrophil-mediated tissue damage ([Trompette 2018](#)). This is of particular importance as viral infections may be accompanied by an aggressive pro-inflammatory response ([Haak 2018](#)) that can elicit a syndrome known as “cytokine storm”.

Kaleido’s orally administered proprietary oligosaccharide mixtures are related to substances found in the human diet that modulate the composition and metabolic output of the microbiome and are generally recognized as safe (GRAS). They allow the controlled production of SCFAs with respect to absolute quantities as well as in relative abundance. Capitalizing on this property, Kaleido has selected a proprietary oligosaccharide mixture, termed KB109, that holds promise in inducing a beneficial profile of SCFA production in the gut while driving the growth of commensal bacteria. Increased SCFA and the modulation in microbiome taxonomy may lead to a more appropriate immune and inflammatory response and may prevent an over-aggressive response, up to and including “cytokine storm” observed in patients with COVID-19.

KB109 is a chemically synthesized oligosaccharide mixture resulting from the polymerisation of glucose:galactose:mannose that has been studied in humans and has been determined to be GRAS for its intended use. It is intended for oral administration and is supplied as a powder to be reconstituted in water. In an *ex vivo* model, KB109 increased the amount of SCFAs produced over water control by approximately three-fold across multiple healthy fecal communities. In addition, it is currently being assessed in an ongoing clinical food study in patients colonized with multidrug-resistant (MDR) organisms to reduce the relative abundance of associated taxa including *Enterobacteriaceae*, *Enterococcus*, and *Clostridium difficile* compared to observational controls (NCT 03944369).

In this study, outpatients with mild-to-moderate COVID-19 illness in the presence and absence of KB109 will be evaluated for its safety and physiologic effects. Physiologic effects will be assessed by measuring biomarkers of inflammation and antibodies as well as physiologic responses of health in patients, quality of life (QOL), and healthcare utilization.

**Study Period:** Up to 47 days (including the Screening period through end of assessments)

| Objective:                                                                                                                                                                   | Endpoint:                                                                                                                                                                                                                                                                                                                                                                                                                                                                                                                                                                                                                                                                                                                                                                                                                                                                                                                                                                                                                                                                                                                                                                                                                                                                                                                                                                                                                                                                                                                                                                                                                                                                                                                                                                                                                                                                                                                                                                                                                                                                                                                                                                                                                                                                                                                                                                                                                                                                                 |
|------------------------------------------------------------------------------------------------------------------------------------------------------------------------------|-------------------------------------------------------------------------------------------------------------------------------------------------------------------------------------------------------------------------------------------------------------------------------------------------------------------------------------------------------------------------------------------------------------------------------------------------------------------------------------------------------------------------------------------------------------------------------------------------------------------------------------------------------------------------------------------------------------------------------------------------------------------------------------------------------------------------------------------------------------------------------------------------------------------------------------------------------------------------------------------------------------------------------------------------------------------------------------------------------------------------------------------------------------------------------------------------------------------------------------------------------------------------------------------------------------------------------------------------------------------------------------------------------------------------------------------------------------------------------------------------------------------------------------------------------------------------------------------------------------------------------------------------------------------------------------------------------------------------------------------------------------------------------------------------------------------------------------------------------------------------------------------------------------------------------------------------------------------------------------------------------------------------------------------------------------------------------------------------------------------------------------------------------------------------------------------------------------------------------------------------------------------------------------------------------------------------------------------------------------------------------------------------------------------------------------------------------------------------------------------|
| 
Primary: To evaluate the safety of KB109 in addition to Supportive Self Care (SSC + KB109) compared to SSC alone in outpatients with mild-to-moderate COVID-19
 | 
 
Number of patients experiencing SP-related treatment-emergent adverse events (TEAEs)
 
                                                                                                                                                                                                                                                                                                                                                                                                                                                                                                                                                                                                                                                                                                                                                                                                                                                                                                                                                                                                                                                                                                                                                                                                                                                                                                                                                                                                                                                                                                                                                                                                                                                                                                                                                                                                                                                                                                                                                                                                                                                                                                                                                                                                                                                                                                                                                    |
| 
Secondary: To evaluate selected measures of health in outpatients with mild-to-moderate COVID-19
                                                               | 
 
Time to resolution of overall 13 COVID-19 related symptoms which is defined as from Day 1 until the day at which the overall composite score of 13 COVID-19 related symptoms becomes 0 or 1 and remains at 0 or 1 for the rest of the Intake Period and for the Follow-up Period. Overall composite score of 13 COVID-19 related symptoms is the sum of 13 COVID-19 related symptom scores (i.e., cough, chills/repeated shaking with chills, muscle pain, fever, headache, anosmia/ageusia, shortness of breath, sore throat, gastrointestinal disturbance/symptoms, diarrhea, fatigue, nasal congestion, and chest tightness (CDC 2020). Each COVID-19 symptom will be recorded by patients on a scale of 0: Absent, 1: Mild, 2: Moderately severe, 3: Very severe. The overall composite score ranges from 0 (no symptoms) to 39 (very severe)
 
Time to resolution of overall 8 cardinal COVID-19 related symptoms which is defined as from Day 1 until the day at which the overall composite score of 8 cardinal COVID-19 related symptoms becomes 0 or 1 and remains at 0 or 1 for the rest of the Intake Period and for the Follow-up Period. Overall composite score of 8 cardinal COVID-19 related symptoms is the sum of 8 cardinal COVID-19 related symptom scores (i.e., cough, chills/repeated shaking with chills, muscle pain, fever, headache, anosmia/ageusia, shortness of breath, and sore throat)
 
Proportion of patients with reduction from Baseline (symptom present at Baseline) in each of 13 individual COVID-19 related symptom at End of Intake Period (EOI) and Follow-up
 
Proportion of patients with symptom becomes absent (symptom present at Baseline) at EOI and Follow-up for each of 13 individual COVID-19 related symptom
 
Change from Baseline to EOI in overall composite score of 13 COVID-19 related symptoms
 
Change from Baseline to EOI in overall composite score of 8 cardinal COVID-19 related symptoms
 
Time to resolution of fever (defined as from Day 1 until the day at which a patient's daily maximum temperature achieves and remains below 100.4 °F for the rest of the Intake Period and for the Follow-up Period without an antipyretic medication)
 
Proportion of patients with oxygen saturation <95% on Day 14 and Day 35
 
Proportion of patients with oxygen saturation <98% on Day 14 and Day 35
 
 |

|                                                                                                                                                                 |                                                                                                                                                                                                                                                                                                                                                                                                                                                                                                                                                                                                                                                                                                                                                |
|-----------------------------------------------------------------------------------------------------------------------------------------------------------------|------------------------------------------------------------------------------------------------------------------------------------------------------------------------------------------------------------------------------------------------------------------------------------------------------------------------------------------------------------------------------------------------------------------------------------------------------------------------------------------------------------------------------------------------------------------------------------------------------------------------------------------------------------------------------------------------------------------------------------------------|
|                                                                                                                                                                 | 
 
Measures collected from the Healthcare Provider Wellness Visits
 
Proportion of patients experiencing hospital admissions during the Intake Period and Follow-up Period (all cause, and COVID-19-related)
 
Healthcare Utilizations during the Intake Period and Follow-up Period
 
                                                                                                                                                                                                                                                                                                                                                                                              |
| Exploratory: To evaluate measures of health in outpatients with mild-to-moderate COVID-19 during the Follow-up Period                                    | 
 
Change from Baseline to the EOI in individual COVID-19 related symptom score: cough, chills/repeated shaking with chills, muscle pain, fever, headache, anosmia/ageusia, shortness of breath, sore throat, gastrointestinal disturbance/symptoms, diarrhea, fatigue, nasal congestion, and chest tightness
 
Individual measures of QOL
 
Change from Baseline to EOI in bedrest time measured as patient-assessed daily cumulative total rest (measured in hours)
 
Proportion of patients with increases in patient global impression on COVID-19 condition (PGIC)
 
Proportion of patients with temperature below 100.4 °F without an anti-pyretic medication
 
 |
| Exploratory: To evaluate the changes in laboratory measures, specific biomarkers, serology and viral load in outpatients with mild-to-moderate COVID-19. | 
 
Change from Baseline (Day 1) in: 
 
Laboratory measures
 
Biomarkers of infection, antibody response, and inflammation (e.g., D-dimer, lipocalin, cytokines, IgM/IgG sero-conversion, and Neutralization Assays)
 
 
 
                                                                                                                                                                                                                                                                                                                                                                                                                      |

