#### **Statistical Methods:**

The study will enroll approximately 350 to 400 patients. The enrollment target is chosen for practical reasons. Assuming a 15% attrition rate, this will provide approximately 296 to 340 evaluable patients (148 to 170 per group). The precision of the point estimate in terms of half-width of the 95% confidence interval (CI) of the AE rate is summarized in [Table 4](#) for a range of evaluable number of patients and assumptions on the SP-related TEAE rates.

The analysis of AEs will be carried out on the Safety Analysis Set ([Section 8](#)). Summaries will be presented by Medical Dictionary for Regulatory Activities (MedDRA) system organ class and preferred term using frequency counts and percentages by group and overall.

The following endpoints will be analyzed based on the Full Analysis Set. The Kaplan-Meier method will be used to estimate median time to resolution of overall 13 COVID-19 related symptoms, overall 8 cardinal COVID-19 related symptoms, fever and resolution rate specific to each group. The change from Baseline to EOI in overall composite score of 13 COVID-19 related symptoms, overall composite score of 8 cardinal COVID-19-related symptoms, and bedrest time will be analyzed using analysis of covariance (ANCOVA) model. Proportion of patients with oxygen saturation <95% (or <98%) will be summarized by group using frequencies and percentages.

The following endpoints will be analyzed based on the Safety Analysis Set. Proportion of patients experiencing hospital admissions (all cause, and COVID-19-related) will be summarized by group using frequencies and percentages. Measures collected from the Healthcare Provider Wellness Visits and Healthcare Utilizations will be summarized by group using the following descriptive statistics: sample size, mean, standard deviation, median, minimum value, and maximum value or using frequencies and percentages.

More details of the statistical methods are provided in [Section 8](#). Methods related to exploratory objectives and supportive analyses will be described in a separate document such as Statistical Analysis Plan (SAP) which will be developed and completed prior to database lock.

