## **Part 2**

Only patients who have a positive test result for COVID-19 can continue to Part 2 of this study. Part 2 of the study comprises an Intake Period and a Follow-up Period. In Part 2, following confirmation of eligibility criteria, the site will notify an independent, third party vendor that a patient is eligible for randomization no later than 48 hours after a positive test result is received by the patient for COVID-19. Upon randomization (SSC + KB109 or SSC alone), a Kaleido at-home Study Kit (KaSK) and SP (KB109) and dosing instructions (as applicable) will be shipped via overnight delivery to the patient's home. The KaSK will include a thermometer, a pulse oximeter, and telemedicine contact information. Patients should continue to record COVID-19-related symptoms using TrialPace™ until the KaSK is delivered.

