### **Part 2, Intake Period**

The Intake Period (Days 1-14) will begin the morning after receipt of the KaSK. All patients will continue to follow the SSC guidance as provided by the treating healthcare provider throughout study participation. In the Intake Period, all patients will continue to record their daily COVID-19-related symptoms, selected COVID-19 signs, responses to questions related to QOL measures, healthcare utilization measures, and concomitant medications taken in the previous 24 hours using TrialPace™ where appropriate. Patients randomized to SSC + KB109 will begin consuming KB109 on Day 1 after recording the required information. All KB109 usage will be noted in the patient's SP log. For all patients in both groups, temperature and oxygen saturation will be measured and recorded as needed throughout the day prior to taking anti-pyretic medication.

Wellness visits by telephone call between Day 1 and Day 14 will be conducted to follow-up on the patient's health status, to ascertain compliance with SP usage or completion of TrialPace™ questions, and to reeducate the patient on the importance of adherence to study instructions including SP usage (where applicable). When wellness and telemedicine visits fall on the same day, they will be combined as a telemedicine visit.

On Day 14, all patients will undergo a telemedicine visit where the following will be conducted: an abbreviated physical examination, an assessment of safety and other protocol-specified measures of health, and an evaluation of whether follow-up treatment is recommended due to a deterioration of COVID-19 symptoms. Patients in the SSC + KB109 group will stop taking KB109 on Day 14. If feasible blood samples for clinical chemistries, biomarkers and serological measures of immunity, and nasal/oropharyngeal swabs for quantitative viral load assessments (research purposes only), will be collected; sample collection may occur at the patient's home by a healthcare professional, remotely, or at the study site or clinic.

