## Part 2, Follow-up Period

On Day 15, all patients will enter the Follow-up Period (Days 15 to 35) where COVID-19 signs, symptoms and healthcare utilization indices will be collected weekly in TrialPace™ where appropriate. On Day 14, the Investigator will instruct the patients to stop the intake and return the SP during the Follow-up Period (Days 15 to 35). In addition, wellness visits by telephone call will be conducted on Days 21, 28, and 35 to follow-up on the patient's health status.

On Day 35, all patients will undergo another telemedicine visit where the following will be conducted: an abbreviated physical examination, an assessment of safety and other protocol-specified measures of health, and an evaluation of whether follow-up treatment is recommended. When wellness and telemedicine visits fall on the same day, they will be combined as a telemedicine visit. If feasible blood samples for clinical chemistries, biomarkers and serological measures of immunity, and nasal/oropharyngeal swabs for quantitative viral load assessments (research purposes only) will be collected; sample collection may occur at the patient's home by a healthcare professional, remotely, or at the study site or clinic.

For convenience, standard terms language included in International Conference for Harmonization (ICH) guidance relevant to the conduct of clinical trials are used in this protocol. An example of such a term used in this protocol is "treatment emergent," included in ICH E9. Use of this standard term is not intended to connote treatment with a medicinal product administered (ICH E9 2018).

Throughout the study, safety will be monitored by TEAEs, clinical signs and symptoms, and selected vital signs (i.e., temperature and oxygen saturation). Concomitant medications/supplements will be recorded throughout the study. Any patient experiencing a TEAE, or intolerable GI symptoms will be evaluated by the principal investigator (PI) or telemedicine provider for possible interruption and/or down-titration of SP dose to the previously tolerated level in consultation with the medical monitor.

In the event of significant worsening of COVID-related symptoms or two sequential pulse oximetry readings of <94% within 2 minutes, patients will be instructed to seek medical attention immediately (see [Section 6.7](#)).

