#### **4.3.7 Healthcare Utilization**

From Day 2 onwards, patient-assessed measures of healthcare utilization will be performed every morning upon waking until the end of the study (Intake Period plus Follow-up Period) (Table 1).

Measures will include:

- Prescription Medication Use – recorded as reason, type, dose and frequency
- Over-the-counter Medication Use – recorded as reason, type, dose and frequency
- Supplement Use – recorded as reason, type, dose and frequency
- Emergency room or Urgent Care visit – Rated as Y/N; if Y then reason will be recorded
- Medical provider visit – Rated as Y/N; if Y then reason as well as if this is a visit for a co-existing condition (mental health visit, physical therapy, etc.) will be recorded;
- Hospital stay – Rated as Y/N; if Y then reason will be recorded

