### **5.5 Withdrawal of Patients**

Patients have the right to withdraw from the study at any time for any reason, without giving a reason and without penalty or loss of benefits they are entitled to. The investigator also has the right to withdraw patients from the study if this is in the best interest of the patient.

Patients will be discontinued from the study in the event of any of the following:

- Patient independently withdraws consent from the study (e.g., patient declines further participation in the study)
- PI determines that the patient has developed a concurrent illness, condition, or an AE due to which continued participation in the study and/or SP dosing is considered potentially harmful to the patient and withdrawal is in the best interest of the patient
- Patient discontinues from SP dosing (i.e., due to development of an AE), but continues his/her consent to participate in the study for follow-up only (e.g., for continued collection of AE information)
- Patient failure to comply with study requirements (e.g., failure to properly consume the SP or failure to comply with other protocol-specific assessments) resulting in protocol deviations that make the interpretation of the data not feasible
- Patient becomes pregnant

Patient requires hospitalization due to worsening COVID-19

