## 8.3 Analysis Sets

### 8.3.1 Safety Analysis Set

The Safety Analysis Set will include all randomized patients. Patients will be included in the group based on the fact that whether or not they actually consumed any amount of KB109: patients who actually consumed any amount of KB109 will be in the SSC + KB109 group; otherwise patients will be in the SSC alone group.

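### Hospital admissions between randomization and Day 1 never reach the admission endpoint's numerator, and the protocol names two different analysis sets for its denominator

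*Protocol*

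**What the plan says.** The Synopsis endpoint table and Section 3.2.2 list as a secondary endpoint "Proportion of patients experiencing hospital admissions during the Intake Period and Follow-up Period (all cause, and COVID-19-related"). Section 8.4.3 summarizes it over the same two periods, by frequencies and percentages.

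**When the window opens and closes.** Randomization is a Screening procedure in the Schedule of Assessments. Under Section 4.1, Part 2, the kit is sent upon randomization and "will be shipped via overnight delivery". Then "The Intake Period (Days 1-14) will begin the morning after receipt of the KaSK". The window closes at Day 35: "On Day 15, all patients will enter the Follow-up Period (Days 15 to 35").

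**Where admissions are recorded.** The diary asks about hospital stays under Section 4.3.7: "From Day 2 onwards, patient-assessed measures of healthcare utilization will be performed every morning upon waking". Separately, inpatient hospitalization is a serious adverse event (Section 7.4.1), collected from consent to the end of follow-up (Section 7.4.3). Section 7.4.4 dates such an event at hospital admission.

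**What happens to the patient.** Section 5.5 lists among the reasons for discontinuation "Patient requires hospitalization due to worsening COVID-19".

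**Which patients are analysed.** The Synopsis, under Statistical Methods, states "The following endpoints will be analyzed based on the Safety Analysis Set" and names hospital admissions first. Section 8.3.1 says "The Safety Analysis Set will include all randomized patients" and assigns the group by whether any KB109 was consumed. Section 8.4.3 instead makes the Full Analysis Set the default for non-AE endpoints unless it says otherwise, and names no other set for admissions. In its next paragraph it does name the Safety Analysis Set for wellness-visit and healthcare-utilization measures. Section 8.3.2 limits the Full Analysis Set to patients with a Baseline and at least one post-Baseline observation in the Intake Period.

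**The concern.** A randomized comparison of admissions should start at randomization. Here it starts when a parcel has arrived and a night has passed. An admission in between belongs to neither named period, and the diary, which starts on Day 2, was not yet asking. The same event would appear in the serious adverse event table and be absent from the hospital-admission endpoint of the same report.

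The denominator adds a second problem. One section keeps the early-admitted patient as a non-event, possibly in the wrong arm. The other normally removes a patient admitted for COVID-19, because the admission itself prevents the Intake observation that the set requires. The protocol does not say which governs, so two analysts could report different proportions from the same data.

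Admissions are a clinically weighty endpoint, probably with few events, so one misplaced patient can be visible in the table.

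**Working it through.** **The plan's own figures.** The protocol states no admission rate and no calculation for this endpoint. Its only sample-size arithmetic is the evaluable number after 15% attrition. 350 × 0.85 = 297.5, or 148.75 per group, stated as 148 (296 in total). 400 × 0.85 = 340, or 170 per group. Both reproduce, and neither bears on this point.

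**Length of the gap.** Kit sent at randomization, delivered overnight, Day 1 the following morning: about 2 days. I take 1 to 3 days as an assumed range.

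**Tracing a patient admitted for worsening COVID-19 in the gap:**

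1. Numerator: the admission precedes the Intake Period, so it is not counted under either analysis set.
2. Denominator per the Synopsis: all randomized patients, so the patient stays in and is counted as not admitted. If randomized to KB109 and no product was taken, the patient is shown under SSC alone.
3. Denominator per Section 8.4.3: discontinued before Day 1, so normally no post-Baseline Intake observation, and the patient drops out of the Full Analysis Set.

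A patient admitted in the gap for another cause need not be discontinued under Section 5.5. If that patient goes on to give Intake data, both sets count the patient as not admitted on the all-cause endpoint.

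**Share uncounted.** With a constant hazard over g + 35 days, the share is g/(g + 35): 1/36 = 2.8%, 2/37 = 5.4%, 3/38 = 7.9%.

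**Number uncounted, 2-day gap, assumed admission rate 2% to 6%.** Low end: 0.02 × 175 = 3.5 admissions per arm; 3.5 × 2/37 = 0.19. High end: 0.06 × 200 = 12 per arm; 12 × 2/37 = 0.65. Over gaps of 1 to 3 days the extremes are 3.5 × 1/36 = 0.10 and 12 × 3/38 = 0.95. If instead every admission fell evenly in the first 10 days, the 2-day figures would be 3.5 × 2/10 = 0.7 and 12 × 2/10 = 2.4. That clustering is a further assumption.

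**Effect of each rule, by illustration.** Take 200 randomized per arm, 6 admissions per arm on Days 1 to 35, and 2 per arm in the gap, for COVID-19 and with no product taken. These counts are chosen to show the mechanics, not predicted.

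| Rule | SSC alone | SSC + KB109 |
|---|---|---|
| As written, Safety Analysis Set | 6/202 = 2.97% | 6/198 = 3.03% |
| As written, Full Analysis Set | 6/198 = 3.03% | 6/198 = 3.03% |
| From randomization, all randomized, by randomized group | 8/200 = 4.00% | 8/200 = 4.00% |
| From randomization, but grouped by consumption | 10/202 = 4.95% | 6/198 = 3.03% |

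The first two rows understate the proportion in both arms by about one percentage point and leave the contrast almost unchanged. The last row turns equal arms into an apparent advantage for KB109, because the two pre-dose admissions of KB109-randomized patients move to SSC alone.

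**The case against.** The case for leaving the text alone has four parts.

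- **The events are not lost.** They are collected as serious adverse events from consent and summarized in their own table, and AE review runs throughout the study. This is correct. It limits the defect to one descriptive proportion, but it also means the correction needs no new data.
- **The effect is small and common to both arms.** Both arms receive kits, no product is taken before Day 1, and Section 5.2 excludes patients judged likely to need hospitalization, on oxygen, or breathless at rest. The endpoint is summarized without a test. All of this stands. A reader might infer that the gap biases the comparison between arms; the documents do not support that.
- **Day 1 is the start for other secondary endpoints.** Section 3.2.2 runs symptom and fever resolution from Day 1. That is consistent, but those endpoints depend on diary baselines, whereas an admission after randomization is an outcome whether or not the kit has arrived. Section 8.4.3 itself counts treatment-emergent events in the SSC group from randomization.
- **The statistical section removes the false non-event.** A reader of the Synopsis might infer that every early-admitted patient is scored as not admitted. Section 8.4.3 does not support that as a general statement: on its default set, a patient discontinued for a COVID-19 admission before Day 1 normally leaves the denominator. This objection succeeds against the stronger reading. What remains is that the admission is missed either way and that the two sections disagree.

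**Conclusion.** The point holds in a limited form. By the protocol's own definitions, an admission between randomization and Day 1 never enters the numerator, and the Synopsis and Section 8.4.3 point to different denominators. Both follow from the text and need no assumption.

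The size does rest on assumptions: a gap of 1 to 3 days, an admission rate of 2% to 6%, and a constant hazard. On these, about 3% to 8% of post-randomization admissions go uncounted, or about 0.19 to 0.65 per arm for a 2-day gap. Early clustering would raise this. The likely result is a slightly understated proportion in both arms. It does not threaten the trial or alter any stated sample-size figure. It is worth correcting because the correction is cheap and because an incomplete one could do more harm than the present wording.

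**What to change.** In the Synopsis, Section 3.2.2 and Section 8.4.3, define the endpoint as the proportion of patients with a hospital admission (all cause; COVID-19-related) from randomization through Day 35. Use all randomized patients as the denominator and analyse by randomized group, not by consumption. Name this one set in both the Synopsis and Section 8.4.3 so that they agree. Derive admissions from the serious adverse event reports together with the diary.

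Make the window and grouping changes together. Widening the window while keeping the consumption-based grouping of the Safety Analysis Set would assign pre-dose admissions of KB109-randomized patients to SSC alone, as in the last row of the table.

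The cost is wording in three places and one extra derivation that combines two sources already collected. The reported admission proportion may rise slightly.
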